## Abstract

**Background:**

To improve tuberculosis (TB) diagnosis, the World Health Organisation (WHO) has called for a non-sputum based triage test to focus TB testing on people with a high likelihood of having active pulmonary tuberculosis (TB). Various host or pathogen biomarker-based testing devices are in design stage and require validity assessment. Host biomarkers have shown promise to accurately rule out active TB, but further research is required to determine generalisability. The TriageTB diagnostic test study aims to assess the accuracy of diagnostic test candidates, as well as field-test, finalise the design and biomarker signature, and validate a point-of-care multi-biomarker test (MBT).

**Methods:**

This observational diagnostic study will evaluate sensitivity and specificity of biomarker-based diagnostic candidates including the MBT and Xpert® TB Fingerstick cartridge compared with a gold-standard composite TB outcome classification defined by symptoms, sputum GeneXpert® Ultra, smear and culture, radiological features, response to TB therapy and presence of an alternative diagnosis. The study will be conducted in research sites in South Africa, Uganda, The Gambia and Vietnam which all have high TB prevalence. The two-phase design allows for finalisation of the MBT in Phase 1 in which candidate host proteins will be evaluated on stored serum from Asia, South Africa and South America and on fingerstick blood from 50 newly recruited participants per site. The MBT test will then be locked down and validated in Phase 2 on 250 participants per site.

**Discussion:**

By targeting confirmatory TB testing to those with a positive triage test, 75% of negative GXPU may be avoided, thereby reducing diagnostic costs and patient losses during the care cascade. This study builds on previous biomarker research and aims to identify a point-of-care test meeting or exceeding the minimum World Health Organisation target product profile of a 90% sensitivity and 70% specificity. Streamlining TB testing by identifying individuals with a high likelihood of TB should improve TB resources use and, in so doing, improve TB care.

**Trial registration:**

NCT04232618 (clinicaltrials.gov) Date of registration: 16 January 2020.

## Background

Pulmonary tuberculosis (PTB) is still a leading cause of death and places severe pressure on health care systems of low- and middle-income countries [1]. The number of TB cases is not dropping fast enough to reach the 2030 End TB Strategy milestones and the COVID-19 pandemic has further slowed progress [1, 2]. Each year, 3.6 million people with TB still go undiagnosed, and approximately 30% of patients diagnosed with TB are not treated [2]. The high burden of undiagnosed and untreated TB further fuels ongoing transmission [1–3].

TB testing remains costly, imperfect, and of limited accessibility even in high TB prevalence areas. The highly sensitive and specific GeneXpert® MTB/RIF or Ultra (GeneXpert®) [4] has shown great promise for rapid detection of active TB, but the cost is high. Furthermore, GeneXpert® is in practice frequently a central laboratory-based platform rather than point-of-care (POC), and is subject to logistical challenges and loss to follow-up [5]. Liquid culture is even less accessible than GeneXpert®, prone to contamination, and takes 42 days for a negative result [6]. Traditional chest X-rays (CXR) are also unsuitable as rapid diagnostic or screening tools. They are relatively expensive, non-specific and at present, depend on skilled personnel for interpretation.

Active pulmonary TB will only be confirmed in approximately one-third of those that undergo costly and time-consuming testing for TB based on suggestive respiratory symptoms [7]. This represents an inefficient use of sparse and expensive resources. Focussing TB investigation could streamline resource use, thereby improving TB care in overburdened health care systems [8]. The World Health Organisation (WHO) has re-emphasised the need for efficient TB screening and seeks a non-sputum based screening tool to narrow TB testing to those patients with a high likelihood of PTB [8]. Such a test should be appropriate for global use and have comparable validity to the WHO minimum target product profile (TPP) sensitivity of 90% and specificity of 70% [8].

Specific host biomarkers (human proteins and RNA) have been linked with active TB disease [9–16]. These represent attractive targets for integration into non-sputum-based triage tests [8]. Over a series of previous EDCTP-funded studies since 2010, the Triage Consortium have discovered protein biomarkers present in the blood and associated with a high likelihood of active TB disease [7, 11, 17–19]. These have been progressively narrowed to a signature consisting of three biomarkers (CRP, SAA and IP-10). This signature has been preliminarily validated using samples from African people with TB symptoms (unpublished). Further testing is required to see if this signature would achieve global applicability. As it was validated using serum, this signature also needs further evaluation of its validity on fingerstick blood. A further 10–15 protein biomarkers showed promise for the purpose of triaging symptomatic patients, and further analysis of these is needed to yield the smallest, most practical signature [7, 17].

Subsequent to previous EDCTP-funded studies (AE-TBC and Screen-TB), we advance a prototype lateral flow (LF) based quantitative diagnostic to a point-of-care (POC) applicable test to measure multiple TB-associated host protein biomarkers in fingerstick blood [7, 20, 21]. This multi-biomarker test (MBT) assay comprises a single LF-based test device which measures individual concentrations of multiple biomarkers, using a luminescent label [up-converting reporter particle (UCP) technology] for quantitation. MBT results can be assessed on a battery-powered stand-alone portable reader to yield immediate results. The test format is highly flexible in the number and identity of biomarkers that can be analysed. The UCP label is not hampered by the red colour produced by haemolysis of erythrocytes, allowing convenient dilution of collected fingerstick blood using a lysis buffer. In comparison to other fluorescent labels, the UCP reporter is not light sensitive, does not fade and has an infinite lifetime. The device has been tested in a laboratory environment but has had limited field testing.

### Aims

The TriageTB Study primarily aims to validate, field test and refine the MBT test using fingerstick blood, as well as the Cepheid Xpert® TB Fingerstick (Xpert® TB FS), which is based on host RNA expression.

### Objectives

Evaluate promising host protein markers on serum samples from various international sites stored at the Foundation of Innovative Diagnostics (FIND) Biorepository (Phase 1a).Evaluate the MBT strip on serum samples from various international sites stored at the FIND Biorepository (Phase 1a).Enrol participants with symptoms suggestive of active pulmonary TB, perform composite diagnostic workup and classify according to clinical TB status at four international sites. 200 participants during phase 1b and 1000 participants in phase 2.Compare lysed and un-lysed preparation methods for fingerstick blood, and refine the technical format of the MBT test (phase1b).Perform MBT and Xpert® TB FS on fresh fingerstick blood from enrolled participants and compare to gold standard clinical classifications to assess diagnostic accuracy (phase 1b and 2).Store specimens and Chest X-ray images for assessment of accuracy of other diagnostic test candidates, including validation of six transcriptomic signatures which have been associated with active TB (phase1b and 2).Propose combined testing algorithms for efficient TB diagnosis using different modalities.Follow-up participants with confirmed TB to determine treatment outcomes and to collect additional samples for treatment response test discovery and validation (phase 1b and 2).Build capacity by establishing of mentor–mentee partnerships.

## Methods

### Study design

This is an observational diagnostic study which will be undertaken in four research sites in countries with high TB prevalence: Stellenbosch University Bio-Medical Research Institute (SU BMRI), South Africa (Clinical site as well as Sponsor of study); Makerere University School of Medicine, Uganda; MRC Unit, the Gambia at London School of Hygiene and Tropical Medicine, Banjul, The Gambia; and Oxford University Clinical Research Unit, Vietnam. Phase 1a and 1b focus on refining the host protein biosignature and field testing the MBT for refinement and lockdown. Phase 2 focuses on validating the final MBT (Fig. 1).

**Fig. 1 Fig1:**
[figure not shown]
Schematic of study design

During Phase 1a, sensitivity and specificity for active TB will be determined for serum biomarkers (CRP, IP-10, SAA, ferritin and 10–15 other promising candidate biomarkers) using 500 stored serum samples obtained through FIND from diagnostic studies in South Africa, Vietnam and Peru using Luminex and Meso Scale Diagnostics (MSD). Phase 1b will validate the MBT among 50 participants per site (total 200), prior to lockdown of applied host biomarkers and test format. Following Phase 1 will be a break in enrolment for analysis and derivation of a global diagnostic biomarker signature to be incorporated into the MBT for Phase 2. Phase 2 will validate the MBT with the final signature among 250 participants per site (total 1000).

The two consecutive phases of the validation study follow the same study schedule. A cross-sectional validation of the POC diagnostics will be followed by a longitudinal evaluation of participants diagnosed with TB, to evaluate the tests’ ability to monitor treatment response and predict cure at the end of treatment. Samples, data and chest X-ray’s from both phases will be stored at the sponsor site’s biorepository and central server respectively to allow for later evaluation of future candidate tests.

### Eligibility

Phases 1b and 2 have the same eligibility criteria. The study sites will recruit from regional healthcare facilities. Participants who have had previous TB, extra-pulmonary TB in addition to pulmonary TB, drug resistance detected on GeneXpert® Ultra or culture, or other concomitant diseases will be included. People living with, and without, Human Immune-deficiency Virus (HIV) will be enrolled. Written informed consent will be obtained from the participant or parent/guardian and assent will be obtained for minors prior to all procedures.

### Inclusion criteria

Aged 12 to 70 years.Symptoms suggestive of TB disease: cough for ≥ two weeks plus at least one of the following: fever, malaise, weight loss, night sweats, haemoptysis, chest pain or loss of appetite.Appropriate consent ± assent provided.

### Exclusion criteria

Stable permanent residence in study area for less than 3 months; no permanent address or planned relocation in the next six months.Pregnancy or breastfeeding.Hb < 9 g/l.Current systemic steroid use or immune suppression therapy in the past four weeks.On TB treatment or Isoniazid Preventive Treatment (IPT) currently or in the last ninety days.Quinolone or aminoglycoside antibiotic use in the past 60 days.In such circumstances where investigator judges there to be a problem with the validity of the consent (e.g. because of suspected mental impairment) or with completion of study procedures (e.g. because of substance abuse).

### Study schedule

On enrolment, participants will receive a standard TB work-up, consisting of clinical assessment, chest X-ray, and sputum GeneXpert® Ultra, smear and culture for *Mycobacterium tuberculosis* (Mtb). Investigational tests will include fingerstick blood testing with the MBT and Xpert® TB FS; stored urine for future use; serum from venous blood for analysis of additional biomarker signatures using Luminex; and whole blood PAXgene tubes for transcriptomic analysis by Fluidigm.

Participants who test positive for TB will follow the study schedule shown in Table 1. As soon as the diagnosis is made, participants will be recalled to TB Day 0 visit for counselling and referral to the local treatment facility to make the final treatment decision and provide TB care. Participants started on standard 6-month TB treatment at clinics will be followed up for clinical review at weeks 4, 8, and 16, at month 6 for end of treatment evaluation, and then at months 12 and 18 to review for possible recurrence. For confirmed TB relapses, Mtb genotyping of baseline and relapse visits will differentiate between relapse and reinfection.

**Table 1 Tab1:** Study schedule for participants with active TB (Phase 1 and Phase 2)

	**Screening/ Enrolment**	**Day 0**^**a**^	**Week** **4**	**Week** **8**	**Week** **16**	**Month** **6**	**Unscheduled/** **TB Relapse 1**	**Month** **12**^c^	**Unscheduled/** **TB Relapse 2**	**Month** **18**
Informed consent/assent	X									
Eligibility criteria	X									
Medical history	X	X	X	X	X	X	X	X	X	X
TB symptoms	X	X	X	X	X	X	X	X	X	X
POC safety tests	X	ICI					ICI		ICI	
HIV-1 testing	X									
Vital signs/directed physical exam	X	X	X	X	X	X	X	X	X	X
Blood sample	X	X	X	X	X	X				
POC FSB tests	X			X	X	X				
Urine	X			X	X	X				
Sputum	X			X^b^	X^b^	X^b^	ICI	ICI	ICI	ICI
Nasopharyngeal swab	X						ICI		ICI	
Chest X-ray	X			ICI		ICI	ICI	ICI	ICI	ICI
Further care provision/referral	ICI	X	ICI	ICI	ICI	ICI	ICI	ICI	ICI	ICI

*FSB* Fingerstick blood, *HIV* Human immune-deficiency virus, *ICI* If clinically indicated, *POC* Point-of-care

^a^TB call-Back

^b^MGIT culture only

^c^Phone-call ± visit if clinically indicated

Participants who do not test positive for TB at screening will be followed up after 8 weeks for clinical review, further testing if required and/or referral to appropriate facilities (Table 2). An unscheduled visit may be conducted before or after the routine week 8 visit for clinical review or repeat investigation.

**Table 2 Tab2:** Study schedule for TB-negative participants (Phase 1 and 2)

	**Screening / Enrolment**	**Unscheduled visit**^**a**^	**Week 8**	**Unscheduled visit**^**a**^
Informed consent/assent	X			
Eligibility criteria	X			
Medical history	X			
TB symptoms	X	ICI	X	ICI
POC safety tests	X	ICI		ICI
HIV-1 testing	X			
Vital signs/directed physical exam	X	ICI	X	ICI
POC fingerstick blood tests	X			
Blood	X			
Sputum	X	ICI	ICI^b^	ICI
Urine	X			
Nasopharyngeal swab	X			
Chest X-ray	X	ICI	ICI^b^	ICI
Provision or referral for further care	ICI	ICI	ICI	ICI

*HIV* Human immune-deficiency virus, *ICI* If clinically indicated, *POC* Point-of-care

^a^An unscheduled visit may be done before or after the Week 8 visit to allow for informing participants of notable results or findings, clinical follow-up ± appropriate referral, repeat or additional investigations as indicated. The decision to complete an unscheduled visit will be at the clinicians’ discretion

^b^Investigations indicated if TB diagnosis is still uncertain at this stage or to evaluate response to treatment received

### MBT format

Figure 2 displays various available MBT formats. The MBT device can hold various sized lateral flow strips, on which each test line detects and quantifies a unique biomarker. One or more standard-sized strips, each with up to three test lines, or one non-standard-sized strip with width determined by the number of parallel slanted test lines, can be used. Standard size would be preferred when considering low cost production utilizing existing production lines from external manufacturers. The ESEQuant LR3 reader (DIALUNOX GmbH, Stockach, Germany) allows for 2D scanning, which has enabled the parallel MBT format. The use of parallel strips, each specific for a single biomarker, minimizes potential cross reactivity. Available standard cassettes can hold 3 parallel strips with standard dimensions, important for industrial production. In phase 1a of the Triage-TB study, performance of the three markers in the Triage Consortium biosignature will be evaluated on a global cohort, using 3-marker MBT strip formats better suited for potential future production. In Phase 1b of Triage-TB, performance of the MBT on fingerstick blood (FSB) will be evaluated and compared to serum. In addition, lysed FSB will be compared to whole FSB. Testing strips for the whole FSB will be provided in a cassette and run horizontally immediately after sampling. Strips for the lysed FSB and serum testing will be provided with microtiter plates to run vertically in the laboratory. A schematic for the approach followed in phase 1B is shown in Fig. 3. For phase 2 of Triage-TB, the chosen MBT format will need to be suitable for industrialisation and for the implementation of the best performing marker combination.

**Fig. 2 Fig2:**

UCP-LF formats. *Figure legend:* Various UCP-LF multi-biomarker test (MBT) formats with distinctive biomarker signatures have been built and evaluated in previous studies [21]. While the structure was initially limited by restrictions of the portable UCP-strip readers, the introduction of a portable reader capable of 2D scan (ESE Quant LR3 version) for use in the TriageTB study allowed the application of the parallel MBT format. The use of parallel strips, each specific for a single biomarker, minimizes potential cross reactivity and each strip has standard dimensions, important for production. Available standard cassettes can hold 3 parallel strips. In this study, for CRP, IP-10 and SAA1

**Fig. 3 Fig3:**
[figure not shown]
Evaluation of fingerstick blood application. *Figure legend:* During Phase 1B of Triage the basic 3-marker MBT strip with CRP, IP-10 and SAA1 will be evaluated and compared to serum. The application of lysed and whole FSB will be compared. For the whole fingerstick blood testing strips were provided in a cassette and run horizontally immediately after sampling; for the lysed fingerstick blood and serum testing strips were provided with microtiter plates to run vertically in the laboratory. The ESE Quant LR3 version will be distributed to all sites for reading

### Gold standard classification

The POC investigational assays will be measured against a composite diagnostic algorithm comprising symptoms, chest Xray findings, sputum GeneXpert® Ultra, TB microscopy, TB culture results, and treatment response (Fig. 4). Potential outcomes are *Definite TB, Probable TB, Possible TB,* and *No TB.* Participants classified as Definite TB or Probable TB will be regarded as gold standard *positive,* and participants with No TB will be regarded as gold standard *negative*. *Definite TB* denotes sputum culture or GeneXpert® Ultra confirmation; *Probable TB* is a combination of radiological or microbiological evidence with a good response to treatment; and *No TB* indicates that all tests are negative for TB and that an alternative diagnosis exists. *Possible TB* occurs in cases with contradicting evidence, often due to loss to follow-up. This category is excluded from analysis because of the uncertainty of TB disease.

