#### Data management and statistics

Data will be entered directly or from paper-source into electronic format using Research Electronic Data Capture (REDCap®). Quality control will include two-step data verification of all forms of data using REDCap® in-built QC capability. The database will also undergo regular central monitoring of key fields by the Sponsor to ensure completeness and accuracy. Classification into gold standard TB Outcome groups will be automated and verified by the attending clinician. Data analysis will be performed by the Stellenbosch University Bioinformatics unit. Basic descriptive statistics will be used to describe the study population. All estimates will be reported with 95% confidence intervals (CI). The main outcomes of interest are the sensitivity, specificity, positive and negative predictive values of the MBT, biomarkers and biosignatures, and algorithmic combinations to differentiate *Definite* and *Probable TB* from *No TB*. These will be analysed using Receiver Operating Characteristic (ROC) curves with Area Under Curve (AUC). There will be a direct comparison of biomarker quantification using the 3-marker MBT and Luminex in Phase 1, determining the reproducibility of the laboratory-based tests and POC tests, using the Kappa statistic for agreement, as well as the performance of the tests in different countries and sub-populations such as those with HIV, previous TB episodes and smear-negative TB. To arrive at the global diagnostic signature, predictive algorithms will be developed using machine learning methods and tested for out-of-sample performance. These will be adapted if the bio-signature requires amendment.

Sample size calculations are for the validation of the MBT in Phase 2, required endpoints being sensitivity, specificity, positive and negative predictive value with 95% CI, with half-width dependent on sample size. For Phase 2, 80 participants (one-third of the 250 per site) are expected to have active TB from previous trial experience, resulting in a target sensitivity of 90% with a 95% CI half-width of 5%. Thus, target precision should be achieved for analysis of MBT performance at each site and overall.

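### As the text defines Definite TB, a positive Ultra alone suffices even in previously treated participants, which can lower measured sensitivity, mainly in the planned previous-TB subgroup

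*Protocol article*

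**What the plan says.** All references are to the protocol article.

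- **Gold standard classification.** The top class rests on either test: "Definite TB* denotes sputum culture or GeneXpert® Ultra confirmation". Probable TB needs radiological or microbiological evidence together with a good treatment response. For analysis, "Participants classified as Definite TB or Probable TB will be regarded as gold standard *positive". On the negative side, "No TB* indicates that all tests are negative for TB and that an alternative diagnosis exists". The remaining class is left out of the analysis: "Possible TB* occurs in cases with contradicting evidence, often due to loss to follow-up". The full algorithm is in Fig. 4, which the text at hand does not show.
- **Eligibility.** The study admits "Participants who have had previous TB, extra-pulmonary TB in addition to pulmonary TB, drug resistance detected on GeneXpert® Ultra or culture".
- **Exclusion criteria.** The only washout for earlier treatment is "On TB treatment or Isoniazid Preventive Treatment (IPT) currently or in the last ninety days", so a person can enter from day 91 after treatment.
- **Data management and statistics.** Performance is to be examined in "sub-populations such as those with HIV, previous TB episodes and smear-negative TB".

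The text has no separate rule for participants with previous TB whose Ultra is positive and whose culture is negative.

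**The concern.** MBT and Xpert TB Fingerstick measure the host response. Ultra is a nucleic-acid test: it shows that mycobacterial DNA is present, not that bacilli are alive. In someone treated for TB some months earlier, the two can part company.

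Suppose such a person has symptoms from another cause, a positive Ultra and a negative culture. A negative index test would then be correct. Under the text's definition it is scored as a missed case of Definite TB. It can never be credited as a true negative, because No TB requires every TB test to be negative.

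The error falls on sensitivity, the figure that matters most for a rule-out test. It is concentrated in the previous-TB subgroup, where the study plans to report performance. A low sensitivity there could come from the test or from the reference rule, and the main analysis alone would not tell them apart.

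**Working it through.** **Step 1: path through the classes.** Take a participant with previous TB, treatment ended 91 days ago, Ultra positive, culture negative, no active disease.

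- Eligible: yes (Eligibility; Exclusion criteria).
- No TB: impossible, since one TB test is positive.
- Definite TB: yes on the words of the definition, since either test suffices.
- Possible TB: conceivable if Fig. 4 treats discordant Ultra and culture as contradicting evidence. The text does not say so.

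The participant is therefore either a reference-positive, as the text reads, or excluded.

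**Step 2: the plan's own precision figure.** The plan expects 80 TB cases per site, so 4 × 80 = 320 overall. At 90% sensitivity the 95% half-width overall is 1.96 × √(0.90 × 0.10 / 320) = 3.3 points. This is the yardstick used below. (With 80 cases at one site the same formula gives 6.6 points, not the stated 5. That is a separate matter and this point does not depend on it.)

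**Step 3: direction.** Let T be true cases, F reference-positives without active disease, and q index-test positivity among those F. With true sensitivity 0.90:

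measured sensitivity = (0.90 × T + q × F) / (T + F)

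This is below 0.90 whenever q < 0.90 and equals 0.90 when q = 0.90.

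**Step 4: illustration.**

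From the document: Phase 2 n = 1000, one-third with TB, sensitivity 90% and specificity 70% (the minimum target profile).

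Assumed, with no source in the document:
- 20% of participants have previous TB, with the same one-third prevalence.
- Ultra is positive and culture negative in 2%, 5% or 10% of previously treated people without TB.
- q = 0.30, that is 1 − 0.70.

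The subgroup has 200 people: T = 66.7, and 133.3 without TB. Overall T = 333.3.

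| Assumed rate | F | Subgroup sensitivity | Overall sensitivity | Overall loss |
|---|---|---|---|---|
| 2% | 2.7 | (60 + 0.8)/69.3 = 0.877 | (300 + 0.8)/336.0 = 0.895 | 0.5 points |
| 5% | 6.7 | (60 + 2.0)/73.3 = 0.845 | (300 + 2.0)/340.0 = 0.888 | 1.2 points |
| 10% | 13.3 | (60 + 4.0)/80.0 = 0.800 | (300 + 4.0)/346.7 = 0.877 | 2.3 points |

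**Step 5: dependence on q.** Write f for the share of reference-positives that are false, so the loss is f × (0.90 − q). At f = 10%, measured sensitivity is 0.84 with q = 0.30, 0.88 with q = 0.70, and 0.90 with q = 0.90.

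**Step 6: against sampling error.** Overall, the loss exceeds 3.3 points only when f is above 0.033 / 0.60 = 5.5% of all reference-positives. None of the three scenarios reaches that. In the subgroup the half-width with 66.7 cases is 1.96 × √(0.09 / 66.7) = 7.2 points, and only the 10% scenario (10 points) exceeds it.

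**The case against.** **The article summarises, and Fig. 4 holds the algorithm.** Fig. 4 or the Possible TB class might absorb discordant results, and the attending clinician verifies the automated class. This stands as a limit on certainty: one cannot say that these participants will in fact be analysed as cases. It does not remove the point. The sentence on Definite TB states a rule, and if Fig. 4 departs from it the two must be reconciled.

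**The mechanism is not in the document.** The article says nothing about residual DNA and calls GeneXpert highly sensitive and specific. That Ultra detects DNA is a property of the assay. How often this yields a positive result without active disease in these participants is unknown, and the rates above are assumptions only. Every participant also has at least two weeks of cough plus another symptom, so index positivity could well be above 30%, which shrinks the bias.

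**Culture is imperfect.** The Background describes it as prone to contamination. Demanding it in the main classification could drop true cases and push measured sensitivity up. This stands, and is why the main reference should be kept.

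**Sensitivity analyses usually belong to the SAP, which is not shown.** Fair. The point rests on the stated rule, not on the absence of an analysis. If the SAP already has one, the fix is largely done.

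**Stronger readings that the documents do not support.**
- A reader might infer from the Table 1 footnote "MGIT culture only" that the plan itself distrusts Ultra after treatment. The footnote concerns monitoring of diagnosed patients at weeks 8 and 16 and month 6, and gives no reason for the choice.
- A reader might infer that the test would miss the 90% target in every scenario. That follows only from starting at exactly 90%, where any loss falls below it. Nor does the article set a pass/fail rule for the subgroup.

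**Conclusion.** The point holds on the text as written. Ultra alone makes Definite TB, including in previously treated people eligible from day 91. Any such participant who is culture-negative and without active disease is then a reference-positive. The bias in sensitivity is downward wherever index positivity in these people is below true sensitivity, and it falls mainly on the previous-TB subgroup.

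Its size cannot be established from the document. Under the assumptions in Step 4, subgroup sensitivity would be about 88 to 80% instead of 90%, and the overall loss, 0.5 to 2.3 points, would lie within overall sampling error. The effect could be smaller, or nil if such participants are rare or index positivity among them is close to 90%. This is a reason to protect the interpretation of the subgroup result. It is not evidence that the overall sensitivity estimate is seriously wrong.

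**What to change.** 1. Keep the composite reference for the main analysis.
2. State in the text, in agreement with Fig. 4, which class an Ultra-positive, culture-negative participant with previous TB enters.
3. Pre-specify a sensitivity analysis of MBT and Xpert TB Fingerstick accuracy, overall and in the previous-TB subgroup. In it, these participants count as positive only if culture-positive or meeting the existing Probable TB rule. Otherwise they are treated as Possible TB and excluded. They are not moved to No TB, because that class requires all tests negative and would put true Ultra-only cases among the negatives.
4. Report the main and sensitivity results side by side, so a reader can see how far a low subgroup sensitivity depends on the reference rule.

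**Cost.** One wording change and one additional analysis. Ultra, culture, medical history and treatment follow-up are already in the study schedule. The sensitivity analysis will have slightly fewer cases and will set aside some true paucibacillary cases. If the index test tends to miss those, that analysis will overstate sensitivity, which is why it should accompany the main result and not replace it.
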